## Abstract

**Background:**

Chronic obstructive pulmonary disease (COPD) impairs quality of life and leads to premature mortality. COPD sufferers experience progressive deterioration of lung function and decreased ability to undertake day-to-day activities. Ginseng has been used for thousands of years in Chinese medicine for respiratory symptoms. Several controlled clinical trials using ginseng for COPD have shown promising clinical effect, however these studies were generally small and with some potential bias, prompting the need for rigorously designed studies.

**Aim:**

The objective of this study is to evaluate the therapeutic value and safety profile of a standardised root extract of Panax ginseng C.A Meyer (ginseng) for symptomatic relief, with a focus on quality of life (QoL) improvements in individuals with moderate (Stage II) COPD FEV1/FVC < 0.7 and FEV_1_ 50% - 80% predicted.

**Methods:**

This paper describes the design of a randomised, multi-centre, double-blind, placebo controlled, two-armed parallel clinical trial. Two trial sites in Melbourne Australia will proportionately randomise a total of 168 participants to receive either ginseng capsule (100 mg) or matching placebo twice daily for 24 weeks. The primary outcomes will be based on three validated QoL questionnaires, St Georges Respiratory Questionnaire (SGRQ), Short Form Health Survey (SF-36) and the COPD Assessment Test (CAT). Secondary outcomes are based on lung function testing, relief medication usage and exacerbation frequency and severity. Safety endpoints include blood tests and adverse event reporting. Intention-to-treat will be applied to all data analyses.

**Discussion:**

Findings from this study may lead to new therapeutic development for chronic respiratory diseases, particularly COPD. This protocol may also guide other investigators to develop quality herbal medicine clinical trials in the future.

**Trial registration:**

Australia and New Zealand Clinical Trials Register (ANZCTR): ACTRN12610000768099

## Background

Chronic obstructive pulmonary disease (COPD) is a major cause of morbidity and mortality worldwide [1]. Current estimates of its prevalence in the adult population (≥ 40 years old) are reported at approximately 10% [2] with global leading cause of death projections ranking COPD 3^rd ^by 2030 [3]. COPD is widely accepted as a preventable disease, but due to continued inhalation of noxious substances, particularly cigarette smoke, COPD is expected to be a major burden for individuals and health care providers for the foreseeable future. Due to limited reversibility and progression, mild symptoms can develop in severity particularly if smoking persists and symptoms are poorly managed. Even after smoking cessation individuals can experience progressive airflow limitation and increased shortness of breath, chronic cough, sputum production and impaired quality of life (QoL). Therefore, early diagnosis and treatment of COPD can reduce the likelihood of symptom deterioration, disease progression and improve overall outcomes [4].

Severity classification of COPD has been defined by the Global Initiative for Chronic Obstructive Lung Disease (GOLD) into four stages, mild (Stage I), moderate (Stage II), severe (Stage III) and very severe (Stage IV). Classification is determined by spirometric measurements using post-bronchodilator forced expiratory volume in 1 sec (FEV_1_) and its ratio to forced vital capacity (FVC) [5]. All stages of COPD, mild to very severe are associated with impaired QoL [6].

Currently there is no cure for COPD. Due to its irreversible nature, conventional treatments primarily intend to control and alleviate symptoms, and to prevent complications. Commonly used treatments include bronchodilators, corticosteroids (for severe cases), and antibiotics (for exacerbations). However, these treatments produce only modest increases in lung function and are associated with a range of adverse effects [7,8]. With improved understanding of the cellular and molecular mechanisms involved in COPD, some novel approaches to treatment are currently under investigation, including pro-inflammatory mediator antagonists, protease inhibitors and phosphodiesterase 4 (PDE4) inhibitors [8]. Yet, for the drugs so far developed, clinical usefulness has been limited by adverse effects [8,9].

Current internationally accepted guidelines recommend symptomatic treatment for COPD with short or long-acting bronchodilators [5]. The addition of regular treatment with inhaled steroids to bronchodilators is only appropriate for more severe symptomatic patients FEV_1 _< 50% predicted (GOLD stages III and IV) and with repeated exacerbations [1]. Although commonly used in mild to moderate COPD patients (GOLD stages I and II) in the community, inhaled steroids are not recommended for this group of patients [5]. It is in this group of symptomatic moderate patients (GOLD stage II), who are often exposed to inhaled steroids without any evidence of benefit, but are at risk of long-term side-effects such as cataracts and osteoporosis, that we seek an alternative and safe treatment approach in this important clinical study.

There is growing interest and use of complementary and alternative medicines for the management of COPD. A recent study in Australia suggested that nearly one in six (17.3%) individuals with COPD had used some form of herbal preparation [10]. Despite increasing use by COPD sufferers, there is inadequate evidence to support routine use of herbal therapies.

Panax ginseng C.A Meyer (ginseng) root is an important Chinese herbal medicine in use for thousands of years. Recently pharmacologically active constituents have been identified, most notably ginsenosides [11]. Potentially relevant activities of these constituents for COPD include, inhibition of pro-inflammatory mediators and cytokines [12], reduction of oxidative stress [13], anti-protease properties [14] and elevation of cAMP [15]. As well as having pharmacologically active constituents, ginseng has an excellent safety profile and is well tolerated by patients [16].

A recent systematic review evaluating ginseng formulae for stable COPD showed promising evidence of lung function and QoL improvements. Included studies had certain methodological weaknesses [17] however these encouraging results prompt the need for rigorously designed randomised controlled trials (RCTs) of high methodological quality.

## Objective

The objective of this study is to evaluate the therapeutic value and safety profile of a standardised root extract of Panax ginseng C.A Meyer (ginseng) for symptomatic relief, with a focus on QoL improvement in individuals with moderate (GOLD Stage II) COPD (FEV_1_/FVC < 0.7 and FEV_1 _50% - 80% predicted). To fulfil the objective, answers to the following questions will be addressed 1) Does a standardised extract of ginseng produce beneficial effects/symptomatic relief in subjects with moderate COPD, in terms of improved QoL and/or improved respiratory function? 2) Does standardised ginseng extract reduce the use of conventional symptom-relief medication in subjects with moderate COPD? 3) With six months treatment and six months follow-up, what are the time courses of onset and persistence of any beneficial effects of the ginseng extract in subjects with moderate COPD? 4) What adverse events does the ginseng extract produce in subjects with moderate COPD?

## Methods

### Design

This study is a randomised, multi-centre, double-blind, placebo-controlled, two-armed parallel clinical trial, comparing a standardised ginseng extract to placebo. The design of the study will integrate rigorous, contemporary clinical research methodology in accord with principles set out in the Declaration of Helsinki and the Good Clinical Practice guidelines with the theory that guides the appropriate use of traditional Chinese medicine in clinical practice. Reporting will be guided by the CONSORT statement [18,19], including relevant intervention extensions relating to herbal medicines [20].

Two hospitals in Melbourne, Australia will randomly assign 168 patients with moderate COPD at a ratio of 1:1 into the ginseng group or matching placebo. Consenting eligible participants will be enrolled for 52 weeks and will be required to attend 6 visits in total. The trial is designed in three phases, 4 weeks run-in; to ensure participants are clinically stable with respect to their COPD, 24 weeks treatment; with either ginseng or placebo capsules, and 24 weeks follow-up (Figure 1).

**Figure 1 F1:**
[figure not shown]
**Participation Flow Chart**.

### Study Duration

Ongoing recruitment will occur for a maximum period of 21 months (October 2010 and June 2012) or until a sample of 168 individuals are randomised.

### Subjects

168 participants will be recruited through local advertising and doctor referrals from hospital outpatients and general practice clinics. Interested participants can telephone or email the trial co-ordinators at the corresponding sites for further information. Participant information and consent forms will be sent to interested individuals to read over prior to scheduling their first visit.

#### Inclusion criteria for participation in the trial

1) males and females aged 40 to 80 years inclusive; 2) ex-smokers (ceased smoking at least three months prior trial entry), and agree to refrain from smoking throughout the trial; 3) satisfy the COPD diagnostic criteria for moderate (stage II) defined by GOLD as post-bronchodilator spirometry, FEV_1_/FVC < 0.7 and FEV_1_ 50% - 80% predicted; 4) are clinically stable, that is, did not experience an acute infective exacerbation of COPD from at least 4 weeks prior to trial entry; 5) meet the Chinese medicine diagnostic criteria for Lung Qi deficiency or Lung and Spleen Qi deficiency; and 6) give written informed consent to participate.

#### Exclusion criteria

1) current smokers; 2) individuals with a diagnosis of alpha_1_-antitrypsin deficiency; 3) a history of asthma or chronic systemic infections or inflammatory conditions in the last three months; 4) pregnancy, breast-feeding or women intending to become pregnant during the course of the study; 5) serious illnesses such as heart, liver or kidney diseases; 6) those who are unable to adequately perform spirometry tests; 7) those taking long-term immunosuppressive agents or immunostimulants; 8) those who have an allergic history to ginseng products; 9) those currently using a ginseng-containing product or have used a ginseng product within the last three months; 10) those who are current users of anticoagulants, anti-hyperglycaemics or monoamine oxidase inhibitor anti-depressants; and 11) those who have undertaken pulmonary rehabilitation within three months of the commencement of the study, or intend to enter pulmonary rehabilitation during the study.

Preliminary screening for eligibility will be undertaken at Visit 1 and during the 4-week run-in period. After this period if suitability continues, participants will be randomly assigned to one of the two treatment groups, ginseng or matching placebo. Continued suitability requires that they be clinically stable and not have experienced an acute infective exacerbation of COPD during the run-in period and that post-bronchodilator spirometry values stay within the moderate (Stage II) range. Individuals who do not meet the preliminary criteria will not be randomised and their participation in the trial will be discontinued. Participants' self-reported respiratory symptoms, smoking status, current medications and other medical conditions will be documented at baseline and throughout.

As well as a conventional diagnosis of COPD performed by a physician, participants must also meet the appropriate Chinese medicine syndrome classifications of Lung Qi deficiency or Lung and Spleen Qi deficiency. A registered Chinese medicine practitioner will perform this diagnosis and only those with either of the two syndromes will be accepted into the study.

### Ethics

This study has been approved by the relevant local human research ethics committees (HRECs) of the participating centres. Any amendments to the study protocol will be submitted to the HRECs for approval. HREC reference numbers: Austin Health HREC/10/Austin/8 (H2010/03892), Eastern Health E90/0910 and RMIT University E31/10.

Clinical trial notification has been filed with the Therapeutic Goods Administration (TGA) Australia (CTN numbers 2010/0449 for Austin Health and 2010/0419 for Eastern Health).

### Randomisation

All eligible subjects will be randomised using two different sizes of block randomisation sequences generated by computer and stratified by site. Treatment allocation numbers will be entered into individually sealed opaque envelopes and provided to each site. At the time of randomisation participants will draw an envelope. Each envelope contains a number that is concealed to the treatment allocation. Randomisation sequence and allocation will be concealed to all study subjects, research staff, investigators and pharmacists until completion of the study. The allocation list will be protected by password access files and held by a non-investigator independent. In the event of an emergency medical situation the individual's randomisation code and group allocation could be identified.

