### Sample size

The sample size calculation is based on the effect size on QoL changes in COPD subjects, in a RCT of one of the most commonly used long-acting beta_2_-adrenoceptor agonists (salmeterol) [21]. In the study, the mean score change on the St Georges Respiratory Questionnaire (SGRQ) was significantly higher (*p *< 0.05) in the treatment group (-6.8 ± 13.2) than in the placebo group (-1.4 ± 11.7) [21]. For the proposed study, to achieve a similar difference between the ginseng extract and placebo treatment groups with an 80% power and a two-tailed significance level of 5%, it is estimated that a sample size of 84 subjects per group will be required, that is, 168 in total. Intention-to-treat analysis will be applied to minimise bias due to drop-outs.

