### Statistical analysis

The trial data will be analysed by an independent biostatistician who will be blinded to the subject allocation. Primary outcome measures SGRQ, SF-36 and CAT scores of participants in the treatment and placebo groups will be assessed at baseline, start of treatment (4 weeks) mid-treatment (16 weeks), end of treatment (28 weeks), mid follow-up (40 weeks) and at the end of follow-up (52 weeks). A suitable statistical package such as SAS will be used to analyse the data. An intention-to-treat analysis will be applied using the Last Observation Carried Forward (LOCF) method. Analysis of covariance with baseline as covariate will be used to assess differences in treatment outcomes between the two groups at each of these time points. To correct for inflated risk of Type 1 error, multiple comparison procedures suggested by Ludbrook et al will be used [25,26]. The use of relief medication during the trial will be investigated for its effect on the outcome measures by using it as a covariate in the statistical analysis. A Data Safety Monitoring Board has been established to assess the progress of the trial, particularly safety endpoints.

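### Site is a stratification factor but is not named in the stated ANCOVA; if site is prognostic, standard errors will be somewhat too large

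*Protocol article*

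**What the plan says.** The Design section of the protocol article sets two centres and equal allocation: "Two hospitals in Melbourne, Australia will randomly assign 168 patients with moderate COPD at a ratio of 1:1". The Randomisation section specifies: "All eligible subjects will be randomised using two different sizes of block randomisation sequences generated by computer and stratified by site".

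The Statistical analysis section gives the model for the comparison of arms: "Analysis of covariance with baseline as covariate will be used to assess differences in treatment outcomes between the two groups". It names one further covariate, for a separate investigation: "The use of relief medication during the trial will be investigated for its effect on the outcome measures by using it as a covariate". Site is not named in either place, and no other section puts it in a model. The article gives no expected split of participants between the hospitals and no between-site difference in any outcome. It does not say whether site is thought to be prognostic.

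**The concern.** Permuted blocks within each hospital keep the two arms almost equal in number at each site. A difference in outcome level between the hospitals therefore contributes almost nothing to the sampling variation of the treatment effect. A model without site still counts that difference as residual error, so the standard error it reports can exceed the true one.

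What is at stake is precision. Confidence intervals would be slightly too wide and p-values slightly too large. The planned sample size gives about 80% power with nothing in hand, so even a small avoidable loss is worth removing.

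**Working it through.** **Inputs from the Sample size section.** SGRQ mean change -6.8 (SD 13.2) against -1.4 (SD 11.7); 84 per group; two-sided 5%; 80% power.

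**Reproducing the plan's figure.**
- Difference: 6.8 - 1.4 = 5.4.
- Pooled SD: sqrt((13.2² + 11.7²)/2) = sqrt(155.565) = 12.47.
- n per group: 2 × (1.960 + 0.842)² × 155.565 / 5.4² = 83.8, rounded up to 84. This matches the plan.
- Standard error at 84 per group: 12.47 × sqrt(2/84) = 1.925. Power is Φ(5.4/1.925 - 1.960) = Φ(0.846) = 80.1%. The t-based value is 79.7%.

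**Assumptions, because the documents give no figure.** Sites are split 50:50, the within-site SD after baseline adjustment is 12.47, and the gap g between the site means after baseline adjustment runs from 0 to 12 SGRQ points. No allowance is made for dropout or for the multiplicity correction.

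**Formulas.**
- Variance that site adds to the residual when omitted: g²/4.
- Ratio of reported to true standard error: r = sqrt(1 + g²/(4 × 155.565)). Equivalently r = 1/sqrt(1 - p), where p is the share of baseline-adjusted variance due to site.
- Type I error with site omitted: 2 × (1 - Φ(1.960 r)).
- Power with site omitted: Φ(5.4/1.925 - 1.960 r). With site included it is 80.1% at every gap.

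Example, g = 8: g²/4 = 16; r = sqrt(171.565/155.565) = 1.050; power = Φ(2.806 - 2.058) = Φ(0.748) = 77.3%.

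| Gap (SGRQ points) | Share p | SE ratio r | Type I error, site omitted | Power, site omitted | Power, site included |
|---|---|---|---|---|---|
| 0 | 0% | 1.000 | 5.0% | 80.1% | 80.1% |
| 2 | 0.6% | 1.003 | 4.9% | 79.9% | 80.1% |
| 4 | 2.5% | 1.013 | 4.7% | 79.4% | 80.1% |
| 8 | 9.3% | 1.050 | 4.0% | 77.3% | 80.1% |
| 12 | 18.8% | 1.110 | 3.0% | 73.6% | 80.1% |

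A 70:30 site split gives slightly smaller effects. At a gap of 8 the ratio is 1.042, type I error 4.1% and power 77.7%.

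**Simulation check.** 168 participants, two equal sites, assumed block sizes 4 and 6, 6,000 runs per setting.
- Gap 0: both models report a mean standard error of about 1.93, against an empirical 1.91 to 1.94.
- Gap 8, site omitted: mean reported standard error 2.03 against an empirical 1.91 to 1.92; type I error 3.6%; power 77.7%.
- Gap 8, site included: mean reported standard error 1.93; type I error 4.6%; power 80.3%.

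The simulation agrees with the formulas in direction and, within simulation error, in size.

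**The case against.** The strongest objection is that the ANCOVA sentence is a one-line summary in a journal article. It says that baseline is a covariate, not that it is the only term, and the same section goes on to name relief medication for a further analysis. The full protocol or the SAP, neither of which is shown, may include site. This stands in part: a reader might infer that site has been deliberately excluded, and the article does not say so. But it is not silent either. It states a model with a named covariate and, elsewhere, a stratification factor, and the two do not match. An analysis plan that followed the published sentence would carry the mismatch forward.

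The second objection is about size, and it stands. A reader might infer that the standard errors will be too large whatever the data show. That holds only if site predicts outcome after baseline adjustment, and nothing in the documents says that it does. Both hospitals are in one city, apply the same Stage II criteria and share uniform spirometry procedures. A site share of 10% of the variance needs a gap of about 8 SGRQ points, which is more than the planned treatment effect of 5.4.

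A reader might also expect adding site to lift power well above the planned level. That requires the borrowed SD of 12.47 to contain the site variance already, which cannot be checked. Even then both models must be put on the same footing: power without and with site is 80.2% and 80.5% at a 1% share, 80.7% and 82.1% at 5%, and 81.4% and 84.1% at 10%. The gain is about 0.3 to 2.7 percentage points.

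Finally, the error is on the safe side, and stratification still balances the arms within site whatever model is fitted.

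**Conclusion.** The point holds in a conditional form and is minor. The randomisation is stratified by site and the stated ANCOVA does not name site. If site is prognostic after baseline adjustment, the analysis will be slightly conservative. For gaps of 2 to 4 SGRQ points the standard error is 0.3% to 1.3% too large and the loss of power is about 0.2 to 0.7 percentage points. It takes a gap of about 8 points to reach 5% and 2.8 points of power. If there is no gap, nothing is lost.

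The treatment estimate is unbiased in every case, type I error stays at or below 5%, and the sample size of 84 per group is unaffected. The omission cannot create a false positive beyond the nominal rate. The figures rest on the assumed 50:50 split, the assumed gaps, and 12.47 as the within-site SD. The ratio depends only on the gap relative to that SD, so a smaller residual SD would make the same gap matter more.

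**What to change.** State in the Statistical analysis section, or confirm in the SAP before unblinding, that site (two levels) enters as a fixed effect alongside baseline in the between-arm ANCOVA models for the three questionnaires and for spirometry.

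The cost is one degree of freedom: with 168 participants, the residual falls from 168 - 3 = 165 to 164. Sample size, data collection and the randomisation scheme do not change. If site turns out not to be prognostic, the loss of precision is negligible: in the simulation with no gap, the reported standard errors with and without site were the same to three decimals.

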### Sample size

The sample size calculation is based on the effect size on QoL changes in COPD subjects, in a RCT of one of the most commonly used long-acting beta_2_-adrenoceptor agonists (salmeterol) [21]. In the study, the mean score change on the St Georges Respiratory Questionnaire (SGRQ) was significantly higher (*p *< 0.05) in the treatment group (-6.8 ± 13.2) than in the placebo group (-1.4 ± 11.7) [21]. For the proposed study, to achieve a similar difference between the ginseng extract and placebo treatment groups with an 80% power and a two-tailed significance level of 5%, it is estimated that a sample size of 84 subjects per group will be required, that is, 168 in total. Intention-to-treat analysis will be applied to minimise bias due to drop-outs.

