### Outcomes

The primary outcome measures will be QoL improvement assessed by using three validated and self-administered questionnaires.

• St Georges Respiratory Questionnaire (SGRQ)

• Short Form Health Survey (SF-36); and

• COPD Assessment Test (CAT)

Participants will complete the three questionnaires at each visit, 6 times in total (Week 0, 4, 16, 28, 40 and 52). (Table 1)

**Table 1 T1:** Measurements to be taken throughout the trial

Visit/Week	1/0	2/4	3/16	4/28	5/40	6/52
**SGRQ**	✓	✓	✓	✓	✓	✓

**SF-36**	✓	✓	✓	✓	✓	✓

**CAT**	✓	✓	✓	✓	✓	✓

**Spirometry**	✓	✓	✓	✓	✓	✓

**Full Blood Count**	✓(Including alpha_1 _antitrypsin)			✓		

**Blood Biochemistry** **KI & LR function**	✓			✓		

CAT: COPD Assessment Test; KI: Kidney; LR: Liver; SF-36: Short Form Health Survey; SGRQ: St Georges Respiratory Questionnaire.

Secondary outcome measures include efficacy and safety components.

Lung function using spirometry indices of FEV_1 _and FEV_1_/FVC ratio.

Use of relief medication short-acting bronchodilator (beta2-agonist Salbutamol)

Frequency, nature and severity of exacerbations

Emergency department presentations and medical practitioner visits

Full blood examination and blood biochemistry for liver and renal function

Adverse event reporting

Spirometry at each site will be conducted using SpiroUSB™ (CareFusion) and Spida5^® ^software. Routine calibration and standard operating procedures will be uniformly undertaken at each site. Participants will be asked to perform spirometry at each visit, 6 times in total (Week 0, 4, 16, 28, 40 and 52). Participants will be advised not to use respiratory medications for several hours prior to their spirometry testing. Two sets of measurements will be taken at each visit, pre-bronchodilator and post-bronchodilator (post 400 μg of inhaled Salbutamol).

Any adverse events will be listed in the trial record and followed-up to completion by the trial co-ordinators and respiratory physicians. Adverse event details will be scored using a six-point scale, 0 = none, 1 = minimal, 2 = mild, 3 = moderate, 4 = severe, and 5 = extremely severe. Participants will be able to report adverse events anytime throughout the trial and will receive advice accordingly. Serious adverse events will be reported to the reviewing HREC and site HRECs within the timeframe specified by the lead HREC.

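### The 80% power is calculated for one uncorrected SGRQ test, but the plan makes three questionnaires primary at every visit and corrects for multiplicity, so 80% is not the power of the planned test

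*Protocol article*

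**What the plan says.** Three sections of the Protocol article bear on this.

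- **Sample size.** The calculation borrows the SGRQ change seen in a salmeterol trial, "in the treatment group (-6.8 ± 13.2) than in the placebo group (-1.4 ± 11.7"), and concludes, "with an 80% power and a two-tailed significance level of 5%, it is estimated that a sample size of 84 subjects per group", that 168 patients are needed in total. No allowance for multiple testing is mentioned.
- **Outcomes.** "The primary outcome measures will be QoL improvement assessed by using three validated and self-administered questionnaires": SGRQ, SF-36 and CAT. None is ranked above the others.
- **Statistical analysis.** The primary scores "will be assessed at baseline, start of treatment (4 weeks) mid-treatment (16 weeks), end of treatment (28 weeks), mid follow-up (40 weeks"). Week 52 closes the list. The arms are compared by ANCOVA, with baseline as covariate, at each of these points. The section then adds: "To correct for inflated risk of Type 1 error, multiple comparison procedures" will be used, identified only by two references. No questionnaire or visit is exempted from the correction, and none is named as decisive.

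**The concern.** A sample size statement should describe the test that decides the trial. Here the power belongs to one SGRQ comparison at the full 5%, whereas the planned analysis is a set of corrected comparisons of which SGRQ at any one visit is only a member. Unless the correction leaves that SGRQ test at 5%, or the ANCOVA gains enough to offset it, the chance of declaring a true 5.4-point benefit is below the stated 80%.

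The protocol also does not say which result settles the question. If the questionnaires or visits disagree, a reader cannot tell from the protocol whether the trial succeeded.

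**Working it through.** **Inputs from the Sample size and Design sections.** Mean SGRQ changes -6.8 and -1.4, so the difference is 5.4. SDs 13.2 and 11.7. Two-sided 5%, 80% power, 1:1 allocation, 84 per arm.

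**Step 1: reproduce the plan's figure.**
- Pooled SD = √((13.2² + 11.7²)/2) = √((174.24 + 136.89)/2) = 12.47.
- n per arm = 2 × (1.96 + 0.8416)² × 12.47² / 5.4² = 83.7, rounded up to 84.

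The stated number is exact for one unadjusted comparison, so it contains no hidden multiplicity allowance. With the noncentral t distribution, 84 per arm gives 79.7% power.

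**Step 2: count the tests.** Six time points are listed. Week 0 opens the run-in and Week 4 is the start of treatment, so neither can show a treatment effect, and baseline is the covariate. Weeks 16, 28, 40 and 52 remain. Three questionnaires at four visits make 12 tests. If the correction ran only across questionnaires at one visit, there would be 3. SF-36 is counted once; using more than one SF-36 score would add tests.

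**Step 3: Bonferroni on change scores (procedure assumed).** The noncentrality is 5.4 / (12.47 × √(2/84)) = 2.81.

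**Step 4: credit the planned ANCOVA.** With equal variances and baseline-to-follow-up correlation r, the change score has variance 2σ²(1 - r) and the ANCOVA residual has σ²(1 - r²). The ratio is (1 + r)/2. The protocol gives no r, so 0.6 to 0.7 is assumed.
- r = 0.6: SD = 12.47 × √0.80 = 11.16, noncentrality 3.14.
- r = 0.7: SD = 12.47 × √0.85 = 11.50, noncentrality 3.04.

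**Step 5: Holm (procedure assumed).** This was simulated with normal test statistics, the same standardised effect on every test, and correlations of 0.3 to 0.8 between tests.

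| SGRQ power, 84 per arm | 3 tests (α/3 = 0.0167) | 12 tests (α/12 = 0.0042) |
|---|---|---|
| Bonferroni, change score | 65% | 46% |
| Bonferroni, ANCOVA, r = 0.7 to 0.6 | 73-76% | 56-59% |
| Holm, change score, equal effects | 73-74% | 58-59% |
| Holm, ANCOVA, r = 0.7 to 0.6, equal effects | 80-85% | 67-74% |

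If only SGRQ responds, Holm on change scores gives about 66% and 48%, close to Bonferroni. A lower r helps more: at r = 0.5, Bonferroni with ANCOVA gives about 79-80% for 3 tests but only 63-65% for 12 (noncentral t and normal approximation respectively).

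All figures assume that every randomised patient contributes to the analysis.

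**The case against.** The strongest reply is that the size of the loss cannot be read from this document. The correction is cited, not described, and the family it covers is not stated. A step-down method sets the SGRQ threshold according to the other p-values, and a fixed sequence led by SGRQ would leave it at the full 5%. A separate statistical analysis plan could specify either. The planned ANCOVA is also more efficient than the change-score comparison used for sizing. This stands, and it is why the result is given as a range. It does not remove the mismatch: the protocol ranks no questionnaire first, exempts no test and keeps the unadjusted calculation.

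A second reply is that power to win on at least one questionnaire may reach 80%. With Holm, 3 tests and equal effects it is about 80-91% even without the ANCOVA gain. That is a different quantity from the one stated, which is power for the SGRQ difference.

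Some stronger readings are tempting but not supported:
- Counting all six listed time points gives 18 tests and power near 41%. Two of those points precede any treatment effect, so 12 is the realistic upper count.
- A reader might infer that familywise error is uncontrolled, at up to 14% for 3 independent tests. That describes a plan without correction, and this plan has one.
- A reader might infer that power is far below 80% on any reading. With 3 tests, Holm and ANCOVA under equal effects, it is not.

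**Conclusion.** The point holds as a mismatch between the stated power and the planned analysis. The 84 per arm is correct arithmetic for a single uncorrected SGRQ test, which is not what the Statistical analysis section plans. That conclusion needs no assumption about the procedure.

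The magnitude does. Across the cases tabulated, SGRQ power for a 5.4-point difference runs from about 46% (12 tests, Bonferroni, no ANCOVA gain) to about 85% (3 tests, Holm, ANCOVA, equal effects on all three questionnaires). It reaches 80% only under the most favourable readings: a family limited to three tests, together with either Holm, ANCOVA and effects on all three questionnaires, or a baseline correlation of about 0.5 or lower. If the family covers the four visits after treatment starts, every case examined falls short, the best being 74%. Confidence is high in the mismatch and moderate in its size.

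**What to change.** **Preferred.** Before unblinding, name SGRQ total score at Week 28 (end of treatment) as the single primary endpoint, tested at two-sided 5%. This matches the sample size calculation, and the stated 80% then applies without extra patients. Make SF-36, CAT and the other visits secondary, and confine the multiplicity procedure to them. Onset and persistence of effect, which the Objective section asks about, remain as secondary questions.

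**If all three questionnaires stay primary.** Name the correction procedure and the exact family of tests. Replace the 80% with the SGRQ power at the resulting significance level under the planned ANCOVA, and state the assumed baseline correlation. Quoting only the 65% figure would not do, because it ignores both the ANCOVA and the multiplicity over visits.

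**Cost.** Either SF-36 and CAT lose primary status, or the stated power will probably be less favourable. The Ethics section sends protocol amendments to the ethics committees, so the change needs their approval and is more than an editorial correction.
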